### Sample size {14}

We determined the required sample size using *PowerUp!* [54], focusing on the primary outcome of maternal psychological distress (Kessler-6) [17] at the 12-month follow-up. Calculations were based on a two-arm cluster-randomized design with equal allocation and equal expected cluster sizes.

Our objective is to achieve 90% statistical power to detect a minimal clinically important difference (MCID), defined as Cohen’s *d* = 0.20, for the primary outcome using a two-tailed significance level (*α*) of 0.05. The parent-reported Kiddy-KINDL^R^ at T2 is specified as a key secondary outcome and will be tested using a hierarchical fixed-sequence procedure: K6 will be tested first at *α* = 0.05, and Kiddy-KINDL^R^ will be formally tested at *α* = 0.05 only if the primary test is statistically significant. This approach controls the overall Type I error rate across the primary and key secondary outcomes without requiring alpha adjustment of the individual tests [55]. While modest, an effect size of this magnitude (*d* = 0.20) is meaningful for a low-intensity, scalable intervention delivered by lay facilitators. In high-burden humanitarian settings, even small average improvements in psychological wellbeing can translate into substantial population-level benefits and policy relevance [56].

For the power calculation, we used an intra-cluster correlation coefficient (ICC) of 0.012, based on the values observed in the earlier SH+ cluster-RCT in the same setting and population [14]. The SH+ intervention is designed for delivery in groups of up to 30 individuals. To account for potential attrition over the 12-month study period, we conservatively assume a 20% dropout rate. Consequently, we plan to recruit 30 mother–child dyads per cluster, with an expected 24 analyzed per cluster at endline. Based on these parameters (power = 0.90, *α* = 0.05, *d* = 0.20, ICC = 0.012, *m* = 24 analyzed per cluster), *PowerUp!* indicates that 24 clusters (12 per arm) are required. This yields a total target sample of 720 mother–child dyads across 24 villages within Rhino Refugee Settlement.

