These calculations are conservative, assuming no variance reduction from baseline adjustment. Because the primary analyses will control for baseline outcome values and cluster-level covariates, realized statistical power is expected to be at least as high as the nominal estimate. Secondary outcomes are not used to determine trial success and are not specifically powered; however, under the same design parameters, this sample size provides reasonable power to detect small-to-moderate effects for continuous secondary outcomes.

We will document actual cluster sizes, attrition, and observed ICCs during implementation and report effect estimates with 95% confidence intervals to reflect the precision achieved.

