## Statistical methods

### Statistical methods for primary and secondary outcomes {20a}

The primary analysis will follow the intention-to-treat (ITT) principle, including all randomized participants in their assigned groups regardless of intervention adherence. The primary outcome is maternal psychological distress (Kessler-6) at 12 months post-intervention (T2). The key secondary outcome is parent-reported child psychosocial wellbeing (Kiddy-KINDL^R^ Parent Report) at T2. To control the overall type I error rate across the primary and key secondary outcomes, we will use a hierarchical fixed-sequence testing procedure: K6 will be tested first at two-sided *α* = 0.05, and Kiddy-KINDLR will be formally tested at two-sided *α* = 0.05 only if the primary test is statistically significant [55]. For the primary and secondary outcomes, we will use linear mixed-effects models (LMM) with random intercepts for villages and participants. The primary estimand for hypothesis testing is the T2 outcome value (final value), with adjustment for the baseline (T0) value of the same outcome when measured at baseline. A pre-specified covariate-adjusted model will be run as a robustness check, additionally adjusting for maternal age and education, child age and sex, household size, and time in the settlement. Results will be presented as adjusted mean differences with 95% confidence intervals and as standardized mean differences (Hedges’ *g*). Outcomes measured at 3 months (T1) will be analyzed analogously as supportive time points to characterize trajectories.

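### The sample-size section puts cluster-level covariates in the primary model and the analysis section does not; separately, the assurance that realised power will reach the nominal 90% is not supported by the stated inputs

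*Protocol article*

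**What the plan says.** Sample size {14} sets the target: "Our objective is to achieve 90% statistical power" for d = 0.20 on the Kessler-6 at 12 months, "using a two-tailed significance level" of 0.05. It takes 24 analysed dyads per cluster after 20% dropout from 30, and states that "we used an intra-cluster correlation coefficient (ICC) of 0.012". It concludes that 24 clusters, 12 per arm, are required. It then calls the calculation conservative because no variance reduction from baseline adjustment was assumed, says that "the primary analyses will control for baseline outcome values and cluster-level covariates", and infers that "realized statistical power is expected to be at least as high as the nominal estimate".

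Statistical methods {20a} gives the primary analysis as a linear mixed model with random intercepts for villages and participants, "with adjustment for the baseline (T0) value of the same outcome when measured at baseline". A second model is labelled a robustness check, "additionally adjusting for maternal age and education, child age and sex, household size, and time in the settlement". The Outcomes {12} section refers the reader to {20a} for the baseline variables that will be controlled for. The abstract speaks only of relevant covariates.

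**The concern.** There are two problems in the same short paragraph of the sample-size section.

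First, the covariate set of the primary model is stated in two ways. One section includes cluster-level covariates. The section that governs the analysis has none, even in its robustness model. The Kessler-6 test at T2 is the primary confirmatory test and it gates the Kiddy-KINDL test, so its covariates should be fixed without ambiguity. With 24 villages, each village-level covariate also costs one of 22 between-cluster degrees of freedom.

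Second, the paragraph tells the reader that power will be 90% or better. If the unadjusted power at the stated inputs is well below 90%, that assurance is wrong as written. A null result at 12 months would then be read as stronger evidence against a lasting effect than the design can supply.

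**Working it through.** **Covariates, side by side.**
- Sample size {14}: baseline outcome and cluster-level covariates, none of them named.
- {20a}, primary model: baseline value of the same outcome.
- {20a}, robustness model: adds maternal age, maternal education, child age, child sex, household size and time in the settlement. All six are person- or household-level.
- No cluster-level covariate is named anywhere in the text. The baseline-outcome part of the two statements agrees; the cluster-level part does not.

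**Inputs for power (all from Sample size {14}).** J = 24 clusters, m = 24 analysed per cluster, ICC = 0.012, d = 0.20 in SD units, two-sided α = 0.05, R-squared = 0. The dropout step is right: 24/0.8 = 30, and 30 × 24 = 720.

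**Formula (two-level cluster-randomised design).** Var = 4 × [ICC(1 − R²c)/J + (1 − ICC)(1 − R²i)/(J·m)], where c is the cluster level and i the individual level. Power comes from the noncentral t with J − 2 − g degrees of freedom, g being the number of cluster-level covariates.

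**The plan's own figure, no covariates.**
- Var = 4 × [0.012/24 + 0.988/576] = 4 × [0.000500 + 0.001715] = 0.00886, so SE = 0.0941.
- Noncentrality = 0.20/0.0941 = 2.12.
- Power = 0.53 (t, 22 df) or 0.57 (normal). The stated 0.90 is not reproduced.
- Minimum detectable effect at 90% power is about 0.32.
- Cross-check: individual randomisation needs 526 per arm. The design effect is 1 + 23 × 0.012 = 1.276, and 526 × 1.276 ≈ 671 analysed per arm. The plan has 12 × 24 = 288. By the t calculation, 58 clusters of 24 would be needed.

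**Variants tried to recover 0.90.**

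| Change from stated inputs | Power (t) |
|---|---|
| One-sided test | 0.66 |
| m = 30 (no dropout) | 0.60 |
| ICC = 0 | 0.63 |
| 48 clusters, m = 24 | 0.84 |
| 48 clusters, m = 30 | 0.89 (normal 0.90) |

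No variant with 24 clusters in total reaches 0.90.

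**What cluster-level covariates can do.**
- One to six that explain nothing: 0.527 falling to 0.515.
- One that removes all between-village variance: Var = 4 × 0.988/576 = 0.00686, SE = 0.0828, power 0.63.

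**What baseline adjustment can do.** The document gives no R-squared, so these values are assumptions, equal at both levels.

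| R² | Power (t) |
|---|---|
| 0.10 | 0.57 |
| 0.20 | 0.62 |
| 0.30 | 0.68 |
| 0.40 | 0.75 |
| 0.50 | 0.82 |
| 0.60 | 0.89 |

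Power of 0.90 needs R² of about 0.61 at both levels, a baseline-to-12-month correlation of about √0.61 = 0.78. If only individual-level variance is explained, it needs about 0.79.

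**The case against.** A reader might infer that, because the cluster-level covariates are missing from {20a}, the power assurance has no basis at all. The document does not support that. The assurance rests on two grounds, and the first, baseline-outcome adjustment, is in the stated primary model. It supports the direction of the claim: power no lower than in the unadjusted calculation. What fails is the level, because the unadjusted calculation gives about 53%, not 90%.

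A reader might also attribute the shortfall to the missing covariates. That is not so either. The gap comes from the inputs and the conclusion drawn from them in the sample-size section, and it exists whichever covariate set is used. At an ICC of 0.012, the choice moves power only between about 0.52 and 0.63.

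Finally, it can be said that {20a} is the designated analysis section, that it fixes one primary model and labels the other a robustness check, and that the sample-size wording is a loose phrase with no variables attached. That is fair: two complete primary models have not been specified. But the article does not defer the question to an analysis plan. It says two things about the same model, and a later plan can agree with only one.

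**Conclusion.** Both parts hold, and they are separate. The covariate set of the primary model is stated inconsistently between Sample size {14} and {20a}. This is a wording conflict with little effect on power, but it concerns the primary confirmatory test and should be settled before T2 data are seen.

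The larger matter is the power statement. At the protocol's own inputs, power is about 0.53 (0.57 by normal approximation). The description of the calculation as conservative, and the expectation that realised power will be at least nominal, are therefore unsupported. They would become true only if covariates explained about 61% of variance at both levels, or about 79% at the individual level alone. The unadjusted figure uses only the document's inputs and the standard two-level formula with equal cluster sizes. The adjusted figures rest on assumed R-squared values and should be read as a range.

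**What to change.** 1. In Sample size {14}, delete the reference to cluster-level covariates, so that the primary covariate set is the one in {20a}, leaving the random effects there as stated. Alternatively, name the cluster-level covariates in {20a} before T2 data are seen and deduct their degrees of freedom.
2. In Sample size {14}, remove the description of the calculation as conservative and the expectation that power will be at least nominal.
3. In the same section, replace the 90% figure, and the statement that 24 clusters suffice for it, with power of about 53% unadjusted. Add the adjusted power for a stated, assumed R-squared, for example 0.68 at 0.30 or 0.82 at 0.50 (equal at both levels).

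The trial status section reports recruitment complete and final follow-up expected in February 2027, so the wording can still be corrected before the primary endpoint data are complete. Enrolment and conduct do not change. The cost is a less favourable stated power.

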### Recruitment {15}

Access to the settlement will be obtained through formal approval from the Office of the Prime Minister (OPM). Following approval, the research team will engage camp authorities to present the study and receive operational feedback. As part of this process, camp authorities will provide updated lists of villages and population estimates, which—together with our predefined village inclusion criteria (see the “Eligibility criteria {10}” section)—will be used to compile the frame of eligible villages. To facilitate recruitment in smaller villages, contiguous villages may be combined to form a single study cluster prior to randomization. An independent researcher not involved in the study will then create a computer-generated randomized list of eligible villages. Our field coordinator will approach village leaders sequentially in that randomized order to invite their village to participate. This process will proceed until 24 clusters (villages or pre-combined units) are included (12 per arm).

We will then convene an inception meeting with village leaders from each of the 24 included clusters, Refugee Welfare Council (RWC) leadership, and OPM representatives to present the trial, discuss implementation logistics, and incorporate feedback. All communications emphasize the voluntary nature of participation, participants’ right to withdraw, and that access to usual services is unaffected by participation or allocation.

Within each selected cluster, we will work in close collaboration with the local RWC representative to prepare a comprehensive roster of residents who meet the study’s individual inclusion criteria. Each roster will be randomized before fieldwork; enumerators will approach prospective participants sequentially in that randomized order, confirm eligibility in a private setting, and obtain informed consent. Recruitment will proceed until 30 mother–child dyads are enrolled per cluster. Households that are ineligible, decline, or cannot be reached will be recorded before proceeding to the next entry.

Assessments will be conducted at the most suitable nearby location to balance privacy, accessibility, and efficiency. Where feasible, this will be within the village; in other cases—particularly for combined clusters—assessments will occur at a nearby central venue serving multiple villages.

Recruitment teams will maintain standardized logs (households approached, screened, consented, enrolled; reasons for ineligibility/refusal; assessment dates and venues) to support CONSORT-compliant reporting and real-time monitoring of accrual against targets. Coordination with camp authorities, village leaders, and RWCs will continue throughout implementation to address local scheduling constraints and logistical issues, while at the same time maintaining adherence to the study protocol and all ethical safeguards.

## Assignment of interventions: allocation

### Sequence generation {16a}

Randomization will occur at the cluster (village or pre-combined village unit) level with allocation performed at a 1:1 ratio to one of two arms: (i) Self-Help Plus (SH+) with Enhanced Usual Care (EUC), or (ii) EUC only. The allocation sequence will be implemented using a sequentially numbered, opaque, sealed envelopes (SNOSE) procedure [57]. An equal number of cards indicating each of the two trial arms will be prepared. These cards will be folded and placed into identical, opaque envelopes, which are then sealed and shuffled. This preparation will be conducted by a collaborator of the local research team who is uninvolved in the recruitment process.

### Concealment mechanism {16b}

Allocation concealment is ensured using the SNOSE method. Opaque, sequentially numbered envelopes will keep the allocation concealed until the moment they are opened, and they will be sealed to make any tampering evident. Because envelopes are indistinguishable and unopened prior to the draw, the allocation is unknown to field staff, RWC collaborators, and participants up to the moment of assignment at the public allocation meeting with village representatives.

### Implementation {16c}

A senior member of the local research team will oversee the allocation process. The allocation itself will be implemented during a central meeting attended by representatives from all 24 participating villages. At this meeting, the procedure will be explained, after which each village representative will publicly draw one sealed envelope at random to determine their cluster’s assignment. This participatory method ensures transparency and community understanding of the randomization process. Once a cluster is allocated, all recruited participants from that cluster are assigned to the corresponding trial arm. Participant enrollment and baseline data collection are conducted prior to cluster allocation.

## Assignment of interventions: blinding

### Who will be blinded {17a}

Because this is a cluster-randomized community trial, blinding of participants and facilitators is not feasible: participants will necessarily be aware of whether they are attending Self-Help Plus (SH+) sessions or receiving Enhanced Usual Care (EUC) only. However, several safeguards are in place to minimize bias in data collection and analysis.

All enumerators, field supervisors, and data entry personnel are blinded to allocation. Enumerators who conduct baseline, 3-month, and 12-month assessments will not be informed of cluster assignment and will have no involvement in intervention delivery.

To prevent unblinding during fieldwork, all intervention activities (SH+ sessions, facilitator meetings, and supervision) are managed by a separate implementation team. This team operates independently of the research staff responsible for screening and outcome measurement. Study databases use coded cluster identifiers, and a master linkage file connecting codes to allocation status is accessible only to the principal investigator and data manager.

### Procedure for unblinding if needed {17b}

Given the low-risk nature of the interventions, we do not foresee any circumstances where unblinding would be required.

## Data collection and management

### Plans for assessment and collection of outcomes {18a}

All data collection will be conducted by trained, Juba Arabic–speaking enumerators who are independent of the SH+ facilitation team. Enumerators will undergo a 5-day intensive training covering ethical procedures, standardized interviewing techniques, task administration, and child engagement strategies. Training will include extensive role-playing, piloting with test participants, and feedback sessions to ensure comprehension and reliability.

Baseline (T0), 3-month (T1), and 12-month (T2) assessments will be conducted at pre-determined venues nearby (see the “Recruitment {15}” section). Enumerators will use tablet-based questionnaires programmed in KoBoToolbox, which includes built-in range checks, skip patterns, and validation rules to minimize data-entry errors. Standard operating procedures (SOPs) will guide all aspects of data collection, including participant identification, consent documentation, and interview termination criteria.

To ensure the cultural validity and clarity of all measures, tools will be translated into Juba Arabic, then refined through piloting with test participants during enumerator training. Feedback from field staff and test participants will inform minor linguistic or contextual adjustments (e.g., colloquial expressions, culturally appropriate child task materials). The full data collection forms are available from the corresponding author upon reasonable request.

Supervisors will conduct random spot checks and daily data reviews to ensure adherence to protocols and assess data completeness. Any inconsistencies will be flagged, reviewed with enumerators, and corrected on the same day. Supervisors will also document field conditions, interruptions, or participant distress events to contextualize data quality.

### Plans to promote participant retention and complete follow-up {18b}

During screening, we exclude individuals who report plans to relocate within the 12-month study period. Participant retention will be supported by regular communication through RWCs and village leaders, flexible scheduling to accommodate livelihood activities, and provision of light refreshments and safe play spaces for children during assessments. To minimize participant burden, the brief 3-month follow-up assessment will be conducted at participants’ homes. At enrollment, we collect multiple contact details for each participant for tracking purposes, including details for alternate contacts who can help locate the participant if temporarily away. Between assessments, we will conduct three brief administrative check-in calls at set intervals to confirm and update contact information, verify anticipated absences, and refresh alternate contact details. Participants who relocate within Rhino Refugee Settlement will be traced via their RWC representative. If a participant moves outside the settlement, where feasible, we will conduct assessments remotely to ensure a more complete dataset for intention-to-treat analyses.

### Data management {19}

Data will be collected and managed using a secure, GDPR-compliant electronic data capture system. Each participant will be assigned a unique study ID; personally identifying information will be stored separately from survey responses. Trained enumerators will enter data directly onto password-protected tablets using the KoboCollect application. This method minimizes data entry errors by enabling real-time validation checks (e.g., for data types and ranges) during data collection.

Data will be uploaded daily from the tablets to a secure, password-protected server hosted by KoboToolbox. To further ensure data quality, the core research team based at Uppsala University will perform daily checks on uploaded records for completeness and identify any inconsistencies or potential errors for immediate follow-up with the field team.

All electronic data will be encrypted both during transmission and while stored. To prevent data loss, regular backups of the dataset will be maintained on a secure, access-controlled server at Uppsala University.

Following trial completion, the cleaned and de-identified dataset will be archived in accordance with Uppsala University’s data governance policies and FAIR data principles. Access to the anonymized dataset for secondary analysis will be granted upon reasonable request and approval by the principal investigator and the relevant ethics committees.

### Confidentiality {27}

All research staff, including enumerators, facilitators, and supervisors, will receive comprehensive training on the importance of maintaining participant confidentiality and data security protocols.

Participant information will be protected at every stage of the study. All electronic data collected via tablets will be password protected and encrypted. All participants will be assigned a unique, non-identifying participant ID number upon enrollment. This ID number will be used on all data collection forms and in the electronic dataset to ensure anonymity.

The file linking participant names to their ID numbers will be stored separately from the main research data. This linking file will be accessible only to a limited number of authorized senior research staff for necessary follow-up and data management purposes.

Consent forms linking names to ID codes will be stored separately in locked filing cabinets at the field office in Uganda, accessible only by the field coordinator.

In all publications and presentations resulting from this research, data will be presented in an aggregated and anonymized format, ensuring that no individual participants can be identified.

